### Procedure for unblinding if needed {17b}

If radiologists note any irregularity or cumulation of cSDH recurrences among trial participants during follow-up, this may lead to unblinding of treatment assignment after consultation of the DSMB.

## Data collection and management

### Plans for assessment and collection of outcomes {18a}

Data will be entered by clinical investigators and supporting trial personnel on electronic case report forms (eCRFs) created by secuTrial®.

Neurological examination comprises the modified Rankin scale for neurologic disability [36], the muscle function according to Janda [37], the presence of word finding disorders, hemiparesis, and anisocoria, as well as vigilance. Standard laboratory parameters will be taken from peripheral blood at baseline and during follow-up. The size and extent of cSDH will be measured on non-contrast CT scans.

The following parameters of recurrence-associated or intervention-associated complications will be documented for study purposes:

Recurrence-associated:Cerebral edemaCerebral infarction

Intervention-associated:Dissection of vessels by the guide wireDislocation of particles or coilsIschemia caused by internal-external vascular connectionsRetinal blindnessEpidural hematoma after MMA perforationInflammation or abscess at the puncture siteVascular fistula at the puncture siteVascular bulging at the puncture siteAllergic reaction to the contrast agentAcute renal failure

Complications not covered by predefined categories may be entered as free text in the eCRF.

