Embolization of the middle meningeal artery (MMA) by polyvinyl alcohol (PVA) particles, liquid embolic agents such as Onyx® (Medtronic, Dublin, Ireland), and/or coiling is a promising interventional adjunct to surgery for cSDH [17, 20, 21], which may also prevent micro-bleeding from cSDH membranes [17]. It has been established as a safe procedure [16, 17, 20, 22–27] in clinical practice for various other indications (e.g., dural arteriovenous fistulas, meningiomas) [28, 29]. Although single cases of cranial nerve palsy and blindness were reported [30, 31], the risk of adverse events may be minimized by excluding anastomoses between intra- and extracranial vessels [32].

Ban et al. conducted an observational study of primary endovascular management of patients with cSDH compared to a historical cohort undergoing the standard of care [20]. Recurrence risks were 1/72 (1.4%) and 129/469 (27.5%), respectively, for an adjusted odds ratio [OR] of 0.056 (95% CI 0.011 to 0.286). Patient selection was conditional on space-occupation by cSDH, with a higher likelihood of surgery with larger blood collections.

The Middle Meningeal Artery Embolization Minimizes Burdensome Recurrence Rates After Newly Diagnosed Chronic Subdural Hematoma Evacuation (MEMBRANE) trial aims at investigating the effectiveness and safety of supportive MMA embolization after surgical evacuation of cSDH.

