**Assessments**						
Demographics, medical history, laboratory data			X			
Neurological tests			X		X	X
Computed tomography			X		X	X
Complications				X	X	X

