### Plans for collection, laboratory evaluation, and storage of biological specimens for genetic or molecular analysis in this trial/future use {33}

Blood drawn from patients at baseline will routinely be analyzed for platelet count, activated partial thromboplastin time (aPTT), and fibrinogen concentration. For study purposes, we will analyze factor XIII concentration by means of STA-R (Stago, Düsseldorf, Germany) with HEXAMATE Factor XIII (Roche Diagnostics, Basel, Switzerland), and the presence of genetic variants F13A1 rs2815822, F13B rs12134960, F13A1 rs2815822 (C > A) and F13B rs12134960 (C > G). To determine factor XIII activity, blood samples will be cryopreserved for later analysis.

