### Adverse event reporting and harms {22}

All SAEs reported by study participants or observed by an investigator within the study period must be documented in the eCRF. SAEs are any undesirable sign, symptom, or medical condition whichIs fatalIs acutely life-threateningRequires or prolongs inpatient hospitalizationResults in persistent or significant disability/incapacityConstitutes a congenital anomaly or birth defect (not applicable, pregnancy excludes from study participation)

The principal investigator will be informed immediately about the onset of a SAE and must decide whether the participant shall be excluded from or remain in the study. The likelihood of a causal relationship between the individual trial intervention and SAE will be investigated further, and patients will be observed until the SAE resolves or a stable condition is reached.

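### Cranial nerve palsy, a harm the rationale names for embolization, has no predefined complication item and no examination item beyond anisocoria; the follow-up laboratory and adverse-event provisions also need reconciling

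*Protocol article*

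**What the plan says.** - **Named harms.** Background and rationale {6a}: "Although single cases of cranial nerve palsy and blindness were reported", followed by the statement that the risk can be reduced by ruling out intra-extracranial anastomoses.
- **Outcome.** Outcomes {12} makes the number and nature of embolization complications up to 3 months a secondary outcome. Section {20a} reports them descriptively, as counts and percentages.
- **Predefined items.** Section {18a} lists ten intervention-associated complications. Retinal blindness and acute renal failure are among them; cranial nerve palsy is not. For anything else: "Complications not covered by predefined categories may be entered as free text in the eCRF".
- **Examination.** The same section lists the mRS, muscle function according to Janda, and "the presence of word finding disorders, hemiparesis, and anisocoria, as well as vigilance".
- **Timing.** Table 1 marks neurological tests at t1, t3 and t4, and complications at t2, t3 and t4. Under {13}, t2 is the embolization visit (intervention arm only, within 72 h of surgery); t3 and t4 fall 1 and 3 months after baseline, each ± 1 week.
- **Laboratory.** Section {18a}: "Standard laboratory parameters will be taken from peripheral blood at baseline and during follow-up". In Table 1 the row "Demographics, medical history, laboratory data" carries one mark, at t1. Section {33}: "Blood drawn from patients at baseline will routinely be analyzed for platelet count, activated partial thromboplastin time (aPTT), and fibrinogen concentration".
- **Adverse events.** Section {22}: "All SAEs reported by study participants or observed by an investigator within the study period must be documented in the eCRF". Section {20a} plans frequencies for adverse events with the word serious in brackets, which implies that non-serious events are counted too.

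**The concern.** The rationale gives two specific neurological harms of the experimental procedure. One (blindness) becomes a predefined item. The other (cranial nerve palsy) does not, although the list is itemised and the outcome it feeds is a stated secondary objective. No listed examination item prompts for it apart from anisocoria, which is at most a partial oculomotor sign.

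A prompted item is answered yes or no for every patient. Free text is filled in only if someone thinks of it, so an empty field does not distinguish an absent palsy from one nobody looked for. Because the result is a raw frequency, a harm that was not sought could appear as zero. The mRS would not necessarily show it, since its grade 1 covers symptoms without significant disability.

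The laboratory and adverse-event mismatches affect the same outcome. They leave unclear whether any laboratory value is scheduled after a contrast procedure for which acute renal failure is a predefined complication, and whether non-serious events are collected in the form in which they are to be tabulated.

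**Working it through.** The protocol states no harm rate or detection rate, so there is no figure of its own to reproduce. The check is mainly textual.

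**1. Recording route for each harm**

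| Harm | Named in {6a} | Predefined in {18a} | Examination or laboratory item named | Other routes |
|---|---|---|---|---|
| Cranial nerve palsy | yes | no | anisocoria only; scope of Janda testing not stated | free text; SAE if serious |
| Blindness | yes | yes (retinal) | none visual | free text; SAE if serious |
| Acute renal failure | no | yes | standard laboratory parameters, analytes not itemised | SAE if serious |

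Only cranial nerve palsy lacks a predefined item.

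**2. Timing.** Neurological tests are at t1, t3 and t4. The order of time points puts t1 before embolization. The first scheduled examination after embolization is therefore t3, about 3 to 5 weeks after baseline (1 month ± 1 week). Complications are assessed at t2, but no neurological test is marked there. A palsy that resolves before t3 would be seen only if it is noticed and written down at t2.

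**3. Laboratory.** Section {18a} says baseline and follow-up; Table 1 says t1 only. Both cannot describe the schedule. The Table 1 row combines laboratory data with demographics and history, which are naturally baseline items, so the row may simply be too coarse. Section {33} concerns specimens for genetic and molecular work, so its short list does not show which analytes count as standard.

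**4. Adverse events.** Section {22} requires SAEs in the eCRF. Section {20a} tabulates adverse events of both kinds. Section {18a} records complications with no seriousness threshold, so the gap is confined to non-serious events that nobody classifies as a complication.

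**5. Illustration of scale.** Let n = 77, the planned size of the embolization arm in {14}; p = true palsy risk; c = share of palsies that reach the data. Both p and c are assumptions. The chance that none is recorded is (1 − p·c)^n.

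| p | c = 100% | c = 75% | c = 50% | c = 40% |
|---|---|---|---|---|
| 1% | 46% | 56% | 68% | 73% |
| 2% | 21% | 31% | 46% | 54% |
| 3% | 10% | 17% | 31% | 39% |

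Example: p = 2%, c = 50% gives (1 − 0.01)^77 = 46%; with c = 100%, (1 − 0.02)^77 = 21%.

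With zero recorded events in 77 patients, the one-sided 95% upper limit is 1 − 0.05^(1/77) = 3.8%. That limit applies to the recorded risk, p·c. It bounds the true risk only if capture is complete.

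**The case against.** The strongest reply is that the protocol already has several nets. Complications are a scheduled assessment at t2, t3 and t4. Unlisted events can go in as free text and serious ones must be recorded. A palsy caused by particles crossing an anastomosis could be entered under the predefined ischemia item for internal-external vascular connections. Janda testing might include facial muscles; the cited source is not available, so this cannot be excluded. The outcome is descriptive and carries no hypothesis test, and the rationale speaks of single cases.

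Most of this stands, and it limits the point. It does not remove it. The ischemia item records a cause, which the assessor must first infer, and does not identify a nerve deficit. Free text is optional. A scheduled complications assessment without a prompt or an examination still relies on recognition.

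A reader might infer more: that blindness and acute renal failure also go unrecorded, that renal function is not measured, and that the safety outcome will under-count harms. The protocol does not support this. Blindness and acute renal failure are predefined items, and new blindness would plausibly meet the disability criterion for an SAE. Section {18a} provides for standard laboratory parameters, and which analytes these are is detail that an article may leave to the full protocol. Nothing in the text gives a palsy risk or a capture rate, so an under-count is possible but not demonstrated.

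**Conclusion.** The point holds in limited form. Cranial nerve palsy is named as a harm of the experimental procedure, but it has no predefined item, no named examination item beyond anisocoria, and no neurological test at the embolization visit. Non-serious or transient palsies may therefore be under-recorded in a secondary safety outcome. Separately, {18a} and Table 1 disagree on follow-up laboratory data, and {22} and {20a} do not match on non-serious adverse events.

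The size of any under-count cannot be derived from the protocol. The zero-event probabilities are illustrative: they assume risks of 1% to 3%, capture of 40% to 100%, and that all 77 patients in the arm are embolized. The full-capture column is an ideal that no visit schedule would reach for transient events. The primary endpoint is unaffected.

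**What to change.** - Add cranial nerve palsy to the predefined intervention-associated complications, with fields for the nerve affected and whether the deficit was transient or persistent.
- Add a brief cranial nerve and visual check at the complication time points already in Table 1 (t2, t3, t4), and one at t1 so that a new deficit can be told from a pre-existing one. Adding it only to the existing neurological tests would leave t2 uncovered. Since t2 exists only in the intervention arm, any between-arm comparison of these findings should rest on t3 and t4.
- Reconcile {18a} with Table 1 on follow-up laboratory data, giving laboratory data its own row, and state which laboratory values, if any, support the acute renal failure item.
- Reconcile {22} with {20a}: either require documentation of non-serious adverse events or restrict the planned tabulation to what is collected.

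Cost: a few eCRF items, a few minutes per visit and some text edits. No new visit is needed.

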### Participant timeline {13}

Participants in the intervention and control groups will undergo five and four scheduled follow-up visits, respectively (Table 1):*−t*_1_ Screening and informed consent*t*_0_ Randomization*t*_1_ Baseline*t*_2_ Embolization (intervention group only, within 72 h after surgery)*t*_3_ Follow-up 1 month after baseline (± 1 week)*t*_4_ Follow-up 3 months after baseline (± 1 week)

**Table 1 Tab1:** Schedule of enrollment, interventions, and assessments

	Study period					
	Enrollment	Allocation	Post-Allocation			Close-Out
Time point	*−t*_*1*_	*t*_*0*_	*t*_*1*_	*t*_*2*_	*t*_*3*_	*t*_*4*_

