## Statistical methods

### Statistical methods for primary and secondary outcomes {20a}

The primary outcome, i.e., reduction in cSDH recurrence through the experimental, surgical plus endovascular treatment, compared to surgery alone, will be analyzed using a chi-square fourfold test for independent samples. The two-sided significance level *α* is set at 5% and the power at 80%. Superiority of the experimental intervention over control is assumed, if the resulting *p*-value is below the nominal significance level of 0.00031 at the time of interim analysis (prompting early trial termination), or the nominal significance level of 0.0469 at the time of final analysis.

Secondary categorical outcomes will be investigated by the Cochran-Mantel-Haenszel (CMH), chi-square, or Fisher’s exact test (if one of the cell frequencies is <5). Recurrence-associated complications, complications associated with endovascular embolization, and (serious) adverse events will be expressed as absolute and relative frequencies.

Exploratory analyses will be performed for the distribution of genetic variants and their correlation (by Pearson’s *phi*-coefficient) with factor XIII deficiency (<70%) across the entire cohort without stratification for the type of intervention. The closer the *phi*-coefficient to 1 or -1, the stronger the association (or predisposition) between genetic variants and factor XIII deficiency. Advanced analyses will be performed to study the association between heterozygous, homozygous, and wild type variants, factor XIII activity, and cSDH recurrence.

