## Discussion

We herein describe the rationale, design, interventions, and methodological framework of a single-center, investigator-initiated, partially blinded, randomized controlled trial to test whether additional endovascular embolization of the MMA is superior to neurosurgical hematoma evacuation only in reducing the rate of recurrence in cSDH.

Current observational evidence suggests that postoperative occlusion of MMA branches may reduce the incidence of recurrent cSDH without major complications. Yet, a randomized controlled trial is urgently needed to evaluate the benefit-to-risk ratio of additional embolization of the MMA compared to the neurosurgical standard of care.

If combined surgical and interventional care turns out to be superior to surgery alone in this trial, this may prompt further confirmatory trials and, at best, may change clinical practice and guideline recommendations.

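### The two named complication outcomes are defined by presumed cause, so comparing arms by heading is not a randomised comparison; SAE reporting closes this gap for serious events only.

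*Protocol article*

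**What the plan says.** Two of the three secondary outcomes in section 12 are complications, one set tied to recurrence and the other to embolization. Section 18a turns this into the list to be collected: "The following parameters of recurrence-associated or intervention-associated complications will be documented for study purposes". Under recurrence stand cerebral edema and cerebral infarction. Under the intervention stand ten items, among them ischemia through connections between internal and external vessels, epidural hematoma after perforation, acute renal failure and several puncture-site events. For the rest, "Complications not covered by predefined categories may be entered as free text in the eCRF".

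Clinical investigators and trial personnel enter the data (section 18a). Section 17a says that blinding the treating specialists and the patients is almost impossible; only the CT readers are described as blinded. Table 1 schedules complications at t2, t3 and t4. Section 13 describes t2 as "Embolization (intervention group only, within 72 h after surgery").

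The analysis section (20a) says: "Recurrence-associated complications, complications associated with endovascular embolization, and (serious) adverse events will be expressed as absolute and relative frequencies". Section 22 adds: "All SAEs reported by study participants or observed by an investigator within the study period must be documented in the eCRF".

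**The concern.** A harm outcome in a randomised trial is interpretable when the same event is counted in the same way in every randomised patient. Here the two named outcomes fix the cause first. A brain infarct in an embolized patient could go under either heading, by the judgement of someone who may know the arm. An infarct in a control patient without recurrence, or renal failure after surgery alone, matches the label of neither heading, and free text is optional. Controls also have no scheduled complication assessment before the 1-month visit.

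The Discussion says that a randomised trial is needed to "evaluate the benefit-to-risk ratio of additional embolization of the MMA compared to the neurosurgical standard of care". If the two headings were read across arms for that purpose, embolization could look protective against infarction while procedure-related infarcts sat under a heading that has no control rate.

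**Working it through.** The plan states no figure for complications, so there is none to reproduce. The check compares the texts and then gives an illustration.

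**Step 1: where each event can be counted**

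| Event | Predefined place (18a) | Cause-neutral place |
|---|---|---|
| Cerebral infarction, cerebral edema | Recurrence heading only | SAE record, if serious |
| Ischemia via vascular connections | Intervention heading only | SAE record, if serious |
| Acute renal failure | Intervention heading only | SAE record, if serious |
| Other, non-serious | None; optional free text | None mandated |

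**Step 2: what the headings do by construction**

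Let R be the recurrence rate and q the infarct risk given recurrence, equal in both arms. Recurrence-associated infarction is R × q. With the planned 30% and 10% (section 14), the ratio of control to embolization is 0.30q / 0.10q = 3 for any q. It repeats the primary endpoint. The embolization heading is zero in controls.

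**Step 3: all infarcts**

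Let b be the infarct risk without recurrence and r the added procedural risk. The values of q, b and r are assumptions; the documents give none.

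- Control: 0.30q + 0.70b
- Embolization: 0.10q + 0.90b + r
- Embolization minus control: r − 0.20(q − b)

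The total is therefore higher with embolization when r > 0.20(q − b).

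With q = 10%, b = 3% and r = 3%:

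- By recurrence heading: 0.30 × 0.10 = 3.0% against 0.10 × 0.10 = 1.0%.
- All infarcts: 0.030 + 0.021 = 5.1% against 0.010 + 0.027 + 0.030 = 6.7%.

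**Step 4: how far this depends on the assumptions**

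The procedural risk r above which the direction reverses is:

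| q | b = 0 | b = 3% |
|---|---|---|
| 5% | 1.0% | 0.4% |
| 10% | 2.0% | 1.4% |
| 20% | 4.0% | 3.4% |

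At q = 10%, b = 3% and r = 1%, the totals are 5.1% against 4.7%, and nothing reverses.

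**Step 5: renal failure**

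If both arms share a background risk k, all-cause rates are k and k. If it were counted only as a complication of embolization, they would read 0 and k.

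**Step 6: numbers of patients**

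With 69 evaluable per arm, 5.1% and 6.7% are 69 × 0.051 = 3.5 and 69 × 0.067 = 4.6 patients.

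**The case against.** The strongest reply is that the headings are not the only count of harm. Section 22 makes SAE documentation mandatory for all participants and looks at cause afterwards: "The likelihood of a causal relationship between the individual trial intervention and SAE will be investigated further". Section 20a tabulates (serious) adverse events separately from the two complication classes. An infarct or renal failure that is fatal, life-threatening or disabling, or that requires or prolongs a hospital stay, is an SAE, so its rate by arm can be recovered. The mRS, which includes death, is also cause-neutral. A reader might infer that complications are counted only by cause and that no arm-neutral rate exists. The documents do not support that reading, and this part of the reply stands in full.

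Second, section 20a expresses complications as frequencies and nowhere announces a claim that embolization reduces infarction. This stands too, although the sentence before it gives tests for secondary categorical outcomes, so a test by heading is not excluded.

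Third, the eCRF and full protocol are not shown, and section 18a does not say that an infarct without recurrence is discarded. That is fair, and no such claim is made here. But the causal definition is in the outcome section of the article itself, and form layout does not change it.

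The SAE route leaves two things open. Only SAEs must be documented, so an infarct seen on CT or a transient renal failure that meets no SAE criterion depends on the headings or on free text. And a sound SAE table does not make the two named outcomes comparable between arms.

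**Conclusion.** The point holds for the two named complication outcomes and for non-serious events. As defined, neither outcome yields an unbiased between-arm rate: one moves with the primary endpoint, the other exists in one arm only, assignment to a heading is not protected by blinding, and t2 adds an assessment that controls lack. This conclusion follows from the text and needs no assumed risk.

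The numerical reversal (3.0% against 1.0% by heading, 5.1% against 6.7% overall) is an illustration. It rests on three assumed risks and, with the other two fixed, needs a procedural infarct risk above 1.4%. A reader might infer that the trial's harm results will point the wrong way. The documents do not support that: the direction depends on unknown risks, and the SAE table would show the serious events.

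**What to change.** Put the events that can occur in both arms on one common list: cerebral infarction or ischemia, cerebral edema, intracranial bleeding, acute renal failure and death. Record them for every randomised patient, serious or not and whatever the presumed cause, over the same period from surgery, with an early assessment in controls to match t2. Define the secondary safety outcome as the proportion with each event, and with any event, by randomised arm up to 3 months. Keep relatedness to recurrence or embolization as a separate descriptive field. Keep purely procedural events (dissection, particle or coil dislocation, puncture-site events, reaction to angiographic contrast) as a description of the embolization arm.

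The cost is a change to the complication list in 18a, a revised outcome sentence in section 12, and one early complication entry for controls, who are within days of their surgery. Unrelated background events will also be counted, which dilutes the contrast slightly. With about 69 evaluable patients per arm the comparison remains descriptive, and the plan should say so.
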